## Abstract

**Abstract:**

**Introduction:**

Interventional clinical trials in recurrent miscarriage use varying expected effect sizes to inform their sample size calculations. Often these are not informed by what stakeholders consider a meaningful treatment effect. Adaptive trial designs may integrate stakeholder views on trial success and futility but the criteria to inform this is lacking. This study aims to understand relevant stakeholder views of what is considered a worthwhile treatment effect for miscarriage prevention interventions and what is acceptable stopping criteria in miscarriage clinical trials.

**Methods and analysis:**

The study is designed as a cross-sectional online anonymous survey. The survey presents different scenarios to respondents relating to varying target differences and probability thresholds and explores success and futility criteria for clinical trials. The survey was developed with personal and public involvement (PPI) through focus groups and a PPI partner. Eligible participants will be those with a personal history of miscarriage, including partners, and healthcare professionals who manage patients who experience a miscarriage. Convenience, snowball and purposive sampling techniques will be employed to invite eligible participants to complete the survey. The survey will be accepting responses for an initial 2-week pilot to check validity, prior to being open for a further 12 weeks. Descriptive analyses and linear regression analyses will synthesise the survey results.

**Ethics and dissemination:**

Ethical approval was obtained from the NHS Research Ethics Committee North West—Greater Manchester East (23/NW/0322) on 30 January 2024. Informed consent will be obtained prior to survey completion. No personal identifying information will be collected. The results will be published in a relevant scientific journal and communicated through our institutional website.

STRENGTHS AND LIMITATIONS OF THIS STUDYStudy findings will impact future clinical trial design, ensuring representation of patient viewpoints and trials designed to identify patient and clinician meaningful treatment differences.This study uses a novel survey instrument for investigating stakeholder views of miscarriage prevention treatment designed in liaison with a personal and public involvement (PPI) partner and PPI input.A pilot phase of the survey will examine survey validity before national dissemination.The survey is only available in English, which may impact the diversity of viewpoints represented.Although some of the questions address how treatment burden may impact stakeholder’s expectations of treatment differences, the range of different potential treatment burdens means this cannot be fully explored.

## Introduction

 Miscarriage prevention is an active area of research driven by pronounced clinical need. Miscarriage, defined as the loss of a pregnancy prior to viability, poses not only physical risks but also significant psychological consequences. Regrettably, miscarriage is common, with 10% of the population experiencing at least one miscarriage and 2% experiencing recurrent miscarriage (RM), defined as two or more losses.^1^

The most common cause of any early pregnancy loss is a chromosomal abnormality of the developing pregnancy.^2^ With higher-order recurring miscarriages, the underlying causes vary and include immunological, haematological and endometrial pathologies.^3^ Approximately 50% of RMs remain unexplained and the search for causes and treatment continues.^4^ Due to this diversity in underlying pathologies, no single treatment to prevent miscarriage can be 100% effective. As new treatment options are developed, robust clinical trials are needed to investigate effectiveness prior to routine introduction.

Interventional clinical trials should be adequately powered to be able to detect a difference between treatments if one exists. These sample size calculations combine different statistical parameters including the target difference or effect size of the treatment.^5^ The target difference may reflect the minimum clinically important difference or be defined by parameters set by the researchers.^6^ The minimum clinically important difference represents the smallest change in treatment outcomes considered clinically meaningful. The target difference is commonly informed by previous evidence, pilot studies or expert opinion and it should be considered an important difference by at least one stakeholder group.^7^ In practice, the target difference may be chosen for convenience with unclear supporting rationale.^7^

While larger trials are required to detect smaller differences, requiring more funding and resources, it is important that the choice of target difference has a clear rationale. The target differences used in previous miscarriage prevention interventional trials vary greatly; with heterogeneity even among large multicentre randomised controlled trials which have aimed to detect treatment differences between 5% and 20%.^8^,^12^

It is estimated that RM patients have a 50%–60% chance of live birth in a future pregnancy without any intervention.^9 11 13^ This figure may increase or decrease depending on previous reproductive history, age and other factors.^14^ At present, it is unknown whether stakeholders’ expectations of treatment would vary at differing probabilities of live birth without intervention.

Consensus on stakeholder views of a meaningful target difference is needed to inform clinical trial design and the interpretation of results. Adaptive trial designs, such as those using a Bayesian framework, may also use stakeholder views on meaningful differences to influence decisions about when to stop a trial early if the trial meets the criteria for success or futility.^15^ This is important because interim analyses may find the treatment difference is very large, making it unethical to continue or that the treatment difference is not enough and that the research is futile. Currently, there are no recommended criteria or relevant clinical literature to inform on the statistical thresholds for stopping or continuing RM trials. Without directly involving the views of stakeholders, researchers cannot presume what should be considered a meaningful intervention.

This is a protocol for an online survey of stakeholders, including people who have experienced miscarriage, their partners and relevant healthcare professionals. The survey would aim to understand stakeholder views on a meaningful target difference and stopping criteria for miscarriage prevention trials. This research would inform future trial design, interpretation of findings and make novel contributions to adaptive trial methodology in this field.

## Methods

### Design

An online cross-sectional survey of stakeholders will be conducted, hosted via the Qualtrics platform. The survey will be anonymous with no personally identifiable information requested.

This study is sponsored by the University of Warwick.

### Participants

Eligible participants include any person or their partners who have experienced miscarriage or healthcare professionals whose job role includes the care of miscarriage patients. The latter includes but is not limited to doctors working within Obstetrics and Gynaecology and nurse specialists in gynaecology, early pregnancy and fertility. There will be no restrictions on gender, ethnicity or social background. While the study does not aim to recruit participants under the age of 18, the survey will be available in the public domain and some respondents that fulfil the inclusion criteria may be below this age. Participant information and the survey will not be available in languages other than English.

### Consent

All participants will be asked to confirm their consent at the start of the online survey (online supplemental material S1). The participants will only gain access to the survey questions if they indicate their consent. As the data collection process is anonymous, it will not be possible to withdraw data from the study. This will be clearly stated on the consent form.

### Setting

The online survey will be hosted by Qualtrics, a cloud-based survey platform. Qualtrics provides a secure and user-friendly interface, allowing participants to access and complete surveys easily. Qualtrics adheres to General Data Protection Regulation and the collection of IP addresses and physical location access will be turned off to allow complete anonymity of respondents.

### Recruitment

Participant recruitment to the survey will be performed through four avenues.

Tommy’s Net (IRAS ID 213470) is a data platform that holds data from patients who have attended Tommy’s national RM clinics, it holds retrospective and prospective data on patient demographics and pregnancy outcomes. It facilitates research into the causes and treatment options for miscarriage patients. On recruitment to Tommy’s Net, patients are asked to consent to be contacted about future relevant research studies. Patients who attended the RM clinic at University Hospitals Coventry and Warwickshire (UHCW), enrolled in Tommy’s Net and consented to be contacted about relevant future research studies will be emailed an invitation to complete this survey. The email invitation will include a link to the participant information sheet. The email will request patients share the invitation with their partners. An estimated 1800 participants are currently registered with Tommy’s Net via the UHCW RM clinic, with most expected to be eligible for recruitment. Although this represents a single centre, referrals to the clinic are received nationally and the cohort is diverse, as previously described.^16^Recruitment posters will be displayed locally at UHCW in relevant departments, including the RM clinic, the early pregnancy unit and the fertility unit. These will be present for the duration of the study.Miscarriage charities will be approached to request dissemination of the survey via their internal platforms, this may include publication on their website, inclusion in any routine newsletters and via social media channels. The Tommy’s charity and The Lily Mae Foundation have already agreed to publicise the survey, with a reach of over 80 000 social media followers.Healthcare professionals who work with miscarriage patients will be identified and contacted directly by email. National networks of relevant clinicians will be approached to request dissemination of the survey.

### Data collection: survey questions

The survey contains 20 questions and has been developed for online completion. The questions were developed by researchers with experience in clinical trials in RM and were presented to a focus group of patients, partners and clinicians held in December 2019. The survey was also reviewed by a personal and public involvement (PPI) partner, [name] from The Lily Mae Foundation. The full survey is available and provided in online supplemental material S1.

The survey is composed of the following sections:

(Section 1) Respondent demographics with identification of respondents who are patients and partners and the number of previous miscarriages they have had or whether they are a healthcare professional and their clinical role.

(Section 2) Introductory scenarios about whether they consider different treatment differences to prevent miscarriage to be worthwhile.

(Section 3) Further scenarios examine the impact of whether additional testing prior to treatment impacts when a treatment difference is considered worthwhile.

(Section 4) Scenarios examining respondent views on clinical trial stopping criteria at differing treatment difference thresholds.

(Section 5) A free text answer on whether the respondent has any other thoughts on what affects whether a treatment to prevent miscarriage is worthwhile.

Visual representations of questions asking for numeric answers on treatment differences have been incorporated to improve question comprehension and survey engagement.^17 18^

The survey will be piloted for 2 weeks to check the face validity of the questions.^19^ The pilot will open locally to participants recruited from UHCW. 250 participants registered with Tommy’s Net will be emailed inviting them to complete the survey. If the response rate to this invitation is less than 10% or the responses indicate issues with question comprehension, the study will be stopped, and the survey questions redesigned with appropriate ethical approval amendments.

### Outcomes

This study aims to understand stakeholder views on a meaningful target difference and stopping criteria for miscarriage prevention trials. The primary outcome will be a meaningful target difference if there is a 50% chance of having a successful pregnancy without the new treatment. Secondary outcomes will look at whether varying the likelihood of successful pregnancy without treatment affects what the respondent considers a meaningful target difference, the effect of investigation invasiveness on consideration of meaningful target difference and thresholds for stopping criteria in clinical trials.

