#### Data analysis plan

The survey will collect quantitative data using numeric responses or multiple-choice questions and there will be one free text answer exploring any other views the respondents wish to share. Quantitative analysis will be conducted using descriptive statistics to summarise the demographic characteristics and survey responses. Means and SD will be calculated for continuous variables, while frequencies and percentages will be produced for categorical variables. Subgroup analyses will be conducted for patients, partners and healthcare professionals using the Kruskal-Wallis statistic to investigate for significant differences in the primary and secondary outcomes results between groups. Linear regression analysis is planned to assess the relationship between demographics including whether a patient, partner or HCP, number of previous miscarriages, HCP role and the primary and secondary outcomes. Where there is greater than 10% missing data for a question, we will perform multiple imputations using the fully conditional specification approach. Qualitative analysis of the free text question will be conducted using thematic analysis through managing software NVivo.

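### Two secondary outcomes ask how a respondent's answer changes between scenarios, but the inferential methods named for them compare only different people

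*Protocol article*

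**What the plan says.** The protocol article, under Outcomes, fixes the reference condition: "The primary outcome will be a meaningful target difference if there is a 50% chance of having a successful pregnancy without the new treatment". It then names three further outcomes. On the first it says: "Secondary outcomes will look at whether varying the likelihood of successful pregnancy without treatment affects what the respondent considers a meaningful target difference". Next comes the influence of how invasive an investigation is on that same judgement, and last "thresholds for stopping criteria in clinical trials".

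The abstract describes the instrument: "The survey presents different scenarios to respondents relating to varying target differences and probability thresholds". Section 3 of the survey is described under Data collection: "Further scenarios examine the impact of whether additional testing prior to treatment impacts when a treatment difference is considered worthwhile". Nothing in the article says that respondents are allocated to different scenarios.

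The Data analysis plan offers three quantitative elements:

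- Descriptive statistics: means and SDs, or frequencies and percentages.
- A comparison of stakeholder groups: "Subgroup analyses will be conducted for patients, partners and healthcare professionals using the Kruskal-Wallis statistic". This is applied to the primary and secondary outcomes.
- A linear regression relating respondent characteristics (stakeholder type, number of previous miscarriages, professional role) to the primary and secondary outcomes.

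No paired test, repeated-measures method or mixed model is named, and scenario is not listed as a regression factor.

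**The concern.** The first two secondary outcomes are effects of changing a condition: the chance of success without treatment, or the invasiveness of the testing. The natural quantity is the change in one person's answer when that condition changes. Both named inferential methods ask something else, namely whether patients, partners and professionals differ, or whether answers vary with respondent characteristics. If everyone raised their answer by the same amount between two scenarios, neither comparison would register it.

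Two things are at stake. First, the change would be reported without a measure of its precision. Second, a non-significant group comparison on a secondary outcome could be misread as evidence that baseline chance or testing does not matter. The Introduction presents the dependence on baseline chance as an open question, and the survey is meant to inform the design of future trials.

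**Working it through.** **Step 1: match each secondary outcome to the named methods.**

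| Secondary outcome | Kind of quantity | Kruskal-Wallis by group | Regression on characteristics | Descriptive statistics |
|---|---|---|---|---|
| Untreated chance of success | change between scenarios | does not test it | does not test it | show it, no interval |
| Invasiveness of investigation | change between scenarios | does not test it | does not test it | show it, no interval |
| Stopping thresholds | a level | group differences only | association with characteristics only | address it |

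The mismatch concerns the first two rows only.

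**Step 2: can the interval be recovered from scenario means and SDs?** If the same n people answer scenarios A and B with a common SD, the mean change is mean(B) − mean(A). Its standard error is SD × √(2(1 − ρ)/n), where ρ is the within-person correlation. The planned summaries do not report ρ. Take n = 250 from the article's minimum sample size and assume SD = 10 points (the article gives none):

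- ρ = 0.3: 10 × √(1.4/250) = 0.75 points
- ρ = 0.6: 10 × √(0.8/250) = 0.57 points
- ρ = 0.8: 10 × √(0.4/250) = 0.40 points

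The same published means and SDs are compatible with all three values, so a reader could not build the interval from them.

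**Step 3: what do the named tests detect?** The article's 250 has no power calculation behind it, so there is no planned figure to reproduce. The behaviour was checked by simulation. The assumptions, none of them from the article except n = 250, were:

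- groups of 170, 30 and 50;
- two numeric scenarios per respondent;
- SD 10 points;
- a uniform shift between scenarios, the same in every group;
- two-sided 5% level;
- 2,000 runs per setting.

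| True shift | ρ | Kruskal-Wallis on the answer | Kruskal-Wallis on the change | Group F-test on the change | Paired Wilcoxon |
|---|---|---|---|---|---|
| 0 | 0.6 | 5.3% | 4.7% | 4.8% | 5.3% |
| 2 | 0.3 | 4.6% | 4.9% | 5.5% | 73.3% |
| 2 | 0.6 | 4.7% | 4.7% | 5.5% | 93.1% |
| 2 | 0.8 | 5.6% | 5.7% | 5.5% | 99.9% |
| 5 | 0.6 | 4.5% | 5.4% | 5.5% | 100% |

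The between-group tests stay at their null rate whatever the shift. That follows from their definition, and the simulation only illustrates it. The paired test on the same data has a type I error of about 5% and high power in most settings.

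**The case against.** The strongest reply has four parts.

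- **Kruskal-Wallis is not misused.** The article calls it a subgroup analysis and gives its purpose as differences between groups. It suits that purpose and is never offered as the test of baseline chance or invasiveness. This stands. The fault is that no method is named for the contrast, while the methods that are named for these outcomes address a different question.
- **The descriptive statistics already estimate the effect.** If the same people answer both scenarios, the difference in means is the mean within-person change. This also stands. A reader might infer that these outcomes get no estimate at all. The text does not support that; what is missing is the interval and the test.
- **The regression could use the change as its dependent variable.** With centred covariates, its intercept would be the mean change with a confidence interval. The wording does not rule this out, and the simulation did not examine the intercept. But the article gives the purpose of the regression as relating respondent characteristics to the outcomes, and it mentions neither a change score nor an intercept.
- **A journal article leaves detail to a fuller plan.** This carries weight against a mere omission. It answers less well here, because the analysis section does assign inferential methods to the secondary outcomes and those methods do not fit two of them.

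The questionnaire supplement is not shown. That each respondent answers every scenario is an inference from the outcome wording and the section descriptions. Whether the answers are numeric or multiple-choice is also unknown. If scenarios were split between respondents, scenario would still have to enter the model, and it is not listed.

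**Conclusion.** The point holds for two of the three secondary outcomes. As written, the effects of baseline chance and of investigation invasiveness would appear as scenario means side by side, with no confidence interval or test for the change. The group comparisons cannot stand in for one. This rests on the reading that the same respondents answer the scenarios. The percentages in the simulation rest on the assumed SD, correlations, shift and group sizes.

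Three stronger readings are tempting but unsupported:

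- **That no secondary outcome is answered.** Stopping thresholds are not worded as a contrast, and descriptive statistics can address them.
- **That the plan wastes a multiple of its sample.** That would require testing scenario means as if they came from independent samples, and the article proposes no such test.
- **That results are distorted by scenario order or by a ceiling on the possible gain.** The article describes neither the order nor the answer scale, so this cannot be judged from it.

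Severity is moderate. The primary outcome, at a 50% untreated chance, is untouched, and the missing analysis can be done on the data the survey already plans to collect.

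**What to change.** In the Data analysis plan, name a within-respondent analysis for the two scenario-contrast outcomes.

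- **Numeric answers:** fit a linear mixed model with scenario as a fixed effect, a random intercept for respondent and a scenario-by-stakeholder-group interaction. Report the mean within-person change with its 95% confidence interval. Use a Wilcoxon signed-rank test (two scenarios) or a Friedman test (more than two) as a rank-based check.
- **Multiple-choice answers:** use a paired categorical analogue.
- **Keep** Kruskal-Wallis and the regression on characteristics for differences between groups, and say that this is their purpose.
- **Optional sensitivity analysis:** if answers are absolute gains, summarise them also relative to the room for improvement, as answer ÷ (100 − baseline). For example, 10 points at the 50% baseline is 10/50 = 20%.

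The cost is a few lines of plan text and slightly more analysis work. It needs no new data, no extra respondents and no change to the questionnaire.

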### Study timelines

The survey is planned to commence on 29 April 2024. It will be open for a 2-week local pilot, followed by national dissemination for 12 weeks. The anticipated close date of the survey is 5 August 2024. It is expected that data analysis and the manuscript will be completed by 1 December 2024.

